#### Intervention

After providing informed consent and authorization, all participants will be randomized using the REDCap randomization function, with equal allocation to two arms: the usual care group or the active referral group.

The usual care group is provided the contact information for 211 if they choose to use it, but 211 does not reach out to these participants. 211 will receive the information of all participants, including those in the usual care group. If a usual care group participant reaches out to 211, they will note this for study records.

211 will reach out to all patients randomized to the active referral group within 48 h of receiving their information via REDCap. The 211 team will discuss the reported social needs with participants and match them with appropriate community resources that can help address their social needs. The 211 teams will also follow up again at 2 weeks with participants to ask if the participant has connected with services and offer additional support connecting to the social service referrals as needed.

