#### Analysis

For the primary outcomes of change in participant level of social need and episode completion, we will use mixed effects modeling, assuming missing at random, to determine if patients who receive community services navigation have greater reduction in social needs and if patients who receive the intervention complete their breast cancer screening episode of care and recommended follow up care. We will examine the interaction between time (conditional on baseline, 6, and 18 months) and intervention. We will analyze the time to follow-up completion using Cox proportional hazard modeling.

For the secondary outcome of community resource use, we will use a similar mixed-effects two-level model and utilize a log link function for a negative binomial regression for the count of social services used. We assume that the number of services will not be normally or dichotomously distributed. For the other secondary outcome of screening behavior, we will use the same mixed-effects two level model with log link function for a negative binomial regression.

Participant demographics will be compared between groups via t-Test and Fisher exact testing, Chi-squared testing, or Wilcoxon-Mann-Whitney test where appropriate.

To determine the sample size, power and sensitivity analyses were conducted with G-Power 3.1. We used a RMANOVA model with 3 total measures as a conservative approach for our mixed-effects model. We assume power = 0.95, alpha = 0.05, and two-tailed significance testing. Results indicate a small effect size (Cohen’s d = 0.09) can be detected. Therefore, recruitment of 1,450 patients with an attrition rate of 20%, will result in an analyzed sample of 1,160, which is sufficient power to detect a clinically meaningful effect. Unpublished pilot data obtained from participants who reported they had a social need the average amount of social needs was 3.06 with a standard deviation = 2.08. We will have 95% power to detect a reduction of social needs to 2.87.

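### The stated 95% power for a fall from 3.06 to 2.87 social needs does not hold for the comparison between arms; at correlations of 0.3 to 0.7 every between-arm test checked falls well short

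*Protocol article*

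**What the plan says.** The last paragraph of the Analysis section in the Protocol article gives the sample-size argument.

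- Model: "We used a RMANOVA model with 3 total measures as a conservative approach for our mixed-effects model".
- Settings: "We assume power = 0.95, alpha = 0.05, and two-tailed significance testing".
- Output: "Results indicate a small effect size (Cohen’s d = 0.09) can be detected".
- Size: "recruitment of 1,450 patients with an attrition rate of 20%, will result in an analyzed sample of 1,160". The Intervention section adds randomisation "with equal allocation to two arms", so 580 per arm are analysed.
- Pilot data: "the average amount of social needs was 3.06 with a standard deviation = 2.08".
- Conclusion: "We will have 95% power to detect a reduction of social needs to 2.87".

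The paragraph does not say which repeated-measures test was run (between, within or interaction), what correlation between visits was assumed, or how the arm difference is expected to develop over time. Aim 1 asks whether navigation lowers social needs relative to referral alone. The Analysis section plans to test this through the interaction of time and intervention at baseline, 6 and 18 months.

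**The concern.** A repeated-measures ANOVA effect size and a difference between two arms in SD units are different quantities. The link between them depends on the test, the number of measures and the pattern of the effect. Multiplying the ANOVA figure by the SD of a single measurement gives a number of needs that is too small, and so a power claim that is too favourable.

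This paragraph is the only sample-size justification in the article. It supports the first of two primary outcomes and the assertion that power is sufficient for a clinically meaningful effect. Someone relying on it could take a null result as strong evidence against a 0.19-need benefit, when the planned test would often miss one.

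**Working it through.** **Inputs from the document.** N = 1,160 (1,450 × 0.8, which reproduces), two equal arms, m = 3 measures, two-sided alpha 0.05, target power 0.95, mean 3.06, SD 2.08, target 2.87.

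**Input assumed.** Within-person correlation ρ. It is not given; 0.5 is used, with 0.3 to 0.7 as the range.

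**Step 1: where 2.87 comes from.** 0.09 × 2.08 = 0.187, and 3.06 − 0.187 = 2.87. In reverse, (3.06 − 2.87)/2.08 = 0.0913.

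**Step 2: where 0.09 may come from.** Noncentral-F power, N = 1,160:

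- Between-groups test, λ = f²·N·m/(1 + (m − 1)ρ). At ρ = 0.5, 95% power needs f = 0.0865, which rounds to 0.09.
- Group-by-time interaction, λ = f²·N·m/(1 − ρ). At ρ = 0.5, 95% power needs f = 0.0471, and 2f = 0.094. Entering f = 0.0913/2 gives 93.6% power.

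Both routes fit, so the text cannot show which was taken. A plain two-sample comparison does not fit: a 0.19-need difference with 580 per arm has 34% power.

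**Step 3: what those f values mean as arm differences.**

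- Between-groups: 2 × 0.0865 × 2.08 = 0.36 needs, averaged over all three measures.
- Interaction, arms equal at baseline and apart by a constant d (in SDs) at 6 and 18 months: f = d/√18, so d = 0.0471 × 4.243 = 0.20 SD, and 0.20 × 2.08 = 0.42 needs.
- Interaction, effect growing linearly (0, d/2, d): f = d/√24, so the final difference is 0.0471 × 4.899 × 2.08 = 0.48 needs.

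None of these is 0.19.

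**Step 4: power for a 0.19-need arm difference (d = 0.0913).** The last two rows use the normal approximation Φ(d√290/√v − 1.96), where d√290 = 1.556.

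| Test | ρ = 0.3 | ρ = 0.5 | ρ = 0.7 |
|---|---|---|---|
| Interaction, constant difference (f = 0.0215) | 25% | 34% | 53% |
| Interaction, linear growth (f = 0.0186) | 20% | 27% | 42% |
| Between-groups, 0.19 at all three measures (f = 0.0457) | 57% | 48% | 41% |
| Baseline-adjusted mean of 6 and 18 months, v = (1 + ρ)/2 − ρ² | 55% | 59% | 74% |
| Same with the 1-month visit added, v = (1 + 2ρ)/3 − ρ² | 65% | 67% | 80% |

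To reach 95%, ρ would have to be about 0.90 for the interaction (constant difference) and about 0.86 for the baseline-adjusted mean of two visits.

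**Step 5: where a figure near 95% does arise.** A before-after fall of 0.19 pooled over all 1,160 women has power of 78%, 91% and 99% at ρ = 0.3, 0.5 and 0.7 with the three-measure within-person test (fall present at both follow-ups). With a paired test it is 75%, 87.5% and 98%.

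**Step 6: arm difference detectable with 95% power.**

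- Interaction, constant difference, f × √18 × 2.08: f = 0.0558, 0.0471 and 0.0365 give 0.49, 0.42 and 0.32 needs at ρ = 0.3, 0.5 and 0.7.
- Baseline-adjusted mean of 6 and 18 months, 3.605 × 2.08 × √(2/580) × √v = 0.440 × √v: 0.33, 0.31 and 0.26 needs.

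**The case against.** **The sentence speaks of a reduction and does not call it a difference between arms.** Read literally as a before-after fall, the power is close to the stated value (step 5). That is a fair reading of the words, but it does not rescue the claim. Aim 1 and the planned interaction both compare arms, and a pooled change includes the usual care group. On this reading the power statement addresses a contrast that the trial does not use to test its hypothesis.

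**The mechanism is inferred.** A reader might conclude that the sponsor certainly mistook Cohen's f for Cohen's d. The document does not establish that. Two different routes give 0.09, and in one of them f has already been doubled into a d-like quantity. What the arithmetic shows is only that the 0.09 was multiplied by the cross-sectional SD to reach 2.87.

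**No single true power can be stated.** A reader might want to replace 95% with one narrow range, or treat 59% (the baseline-adjusted mean of two visits at ρ = 0.5) as the ceiling. The documents support neither. Correlation, test and effect pattern are all unstated. The Outcomes section also lists a 1-month assessment, and using it would lift the baseline-adjusted figure to about 67% at ρ = 0.5. The article also calls its three-measure model conservative. These points widen the range upward, but over correlations of 0.3 to 0.7 nothing exceeds about 80%.

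**Only wording changes.** That is so, and the confidence interval in the final report will show what has been excluded. The figure is still the stated basis for the sample size and is wrong for the primary comparison.

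**Conclusion.** The concern holds: 95% power for a fall to 2.87 does not apply to the comparison between arms. With 1,160 analysed and correlations of 0.3 to 0.7, power for a 0.19-need arm difference runs from about 20% (interaction, linear growth) to about 80% (baseline-adjusted mean of three follow-ups, an analysis the article does not name). For the planned interaction with a constant difference it is 25–53%. The difference that this test detects with 95% power is about 0.42 needs at correlation 0.5, a little over twice the stated 0.19.

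These figures rest on the assumed correlations, an SD of 2.08 at every visit, equal arms, and the effect patterns shown. The source of the 0.09 is probable, not proven. A reader might also infer that the trial is too small. That does not follow, because the document does not say that 0.19 needs is the smallest effect worth detecting on grounds other than this calculation.

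**What to change.** Keep recruitment at 1,450. In the sample-size paragraph:

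1. Name the repeated-measures test, the effect-size metric (f or d), the assumed correlation between visits, and the assumed pattern of the arm difference over time.
2. Replace the 2.87 statement with the between-arm difference detectable by the planned test. For the interaction with a constant follow-up difference, this is about 0.42 needs at 95% power and correlation 0.5, with the range 0.49 to 0.32 over correlations 0.3 to 0.7.
3. Quote the smaller figure of about 0.31 needs (0.33 to 0.26) only if a baseline-adjusted mean of 6 and 18 months is made the primary analysis. Otherwise it would again overstate power for the planned test.
4. Remove the Cohen's d label from 0.09, or relabel the figure correctly once the sponsor has confirmed from the G-Power output what it is.

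The cost is a recalculation, some rewording and a less favourable published figure. No extra patients are needed.

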### Phase 2 - Qualitative analysis

In order to understand the perspectives of health care providers, we will conduct focus group discussions (FGDs) with multidisciplinary providers who work with patients who receive abnormal mammogram results. These discussions will last for about 1.5 h, and participants will be compensated for their time. These interviews will be facilitated by a professional with the Community Collaboration & Engagement Team at the University of Utah. Additionally, these discussions will be viewed by an observer who will note factors like body language in a written report. During these focus groups, we will discuss barriers and facilitators of engagement, barriers in follow-up, community service navigation, and what support may be needed to improve the process.

Additionally, we will randomly select 40 individuals from the RCT for individual in-depth interviews (IDIs) to understand the perspectives of patients who participated in the intervention group. These 40 patients will include: 10 patients who received social services through 211 and completed mammography follow up, 10 individuals who received social services through 211 and did not complete mammography follow up, 10 who did not use utilize 211 and did complete mammography follow up, and 10 who did not utilize 211 *and* did not complete mammography follow up. To capture the unique needs of Spanish-speaking participants, at least half of those interviewed will be individuals who primarily speak Spanish, with certified interpreters available for the interviews as needed.

Audio tapes of the FGDs and IDIs will be transcribed, and then a thematic analysis framework will be implemented.

## Discussion

Previous research has found that women undergoing screening mammography face social and financial barriers such as income, insurance costs, and place of residence [10]. Targeted interventions may help those with social needs and abnormal mammography findings receive appropriate follow-up care by connecting patients with social services [13]. The current study tests the use of a low-cost community service intervention, United Way 211, among participants who report social needs and have received abnormal mammogram results.

Should this intervention help overcome barriers to the follow-up process, we can improve care for those with social needs. If this intervention benefits participants, we can implement a system in which clinicians and other healthcare staff can provide resources for their patients that do not place further burden on the healthcare team by collaborating with community partners. By addressing community barriers to healthcare, we meet patients where they are in their lived contexts. Through this holistic lens, we can support our patients who need it most.

## Data Availability

No datasets were generated or analysed during the current study.
